### 9.3.7 Action Taken for the Study Drug in Response to Adverse Events

The investigator or subinvestigator will record any action taken for the study drug in response to nonserious unsolicited AEs, SAEs, and AEs leading to permanent discontinuation of study treatment or withdrawal from the study that occur after study drug administration in the eCRF, as follows:

- Dose not change: No change in study drug dosage and administration was made.
- Permanent discontinuation: The study drug was permanently discontinued.
- Temporary discontinuation: The study drug was temporarily discontinued.
- Not applicable: The subject died, study drug administration was completed before the reaction/event, or the reaction/event occurred before the start of study drug administration.

### 9.3.8 Other Action Taken for Adverse Events

The investigator or subinvestigator will record any other action taken in response to nonserious unsolicited AEs, SAEs, and AEs leading to permanent discontinuation of study treatment or withdrawal from the study that occur after study drug administration in the eCRF, as follows:

- None
  - No treatment was required.
- Medication required
  - Prescription and/or over-the-counter drugs were required to treat the AE.
- Hospitalization or prolongation of existing hospitalization required

Confidential

- Hospitalization was required or prolonged due to the AE, whether or not medication was required.
- Other

### 9.3.9 Adverse Event Outcome

The investigator or subinvestigator will record the outcome of nonserious unsolicited AEs, SAEs, and AEs leading to permanent discontinuation of study treatment or withdrawal from the study that occur after study drug administration in the eCRF, as follows:

- Recovered/resolved
  - The subject fully recovered from the AE, with no residual effect observed.
- Recovering/resolving
  - The AE has improved but has not fully resolved.
- Not recovered/not resolved
  - The AE itself is still present and observable.
- Recovered/resolved with sequelae
  - Residual effects of the AE are still observed.
  - Sequelae/residual effects are present.
- Fatal
  - "Fatal" should be used when death is a direct outcome of the AE.
- Unknown

## 9.4 Adverse Events of Special Interest

The AEs of special interest are defined as "solicited injection site AE," "solicited systemic AEs," "combined elevations of aminotransferases and bilirubin," and "ADE."

### 9.4.1 Combined Elevations of Aminotransferases and Bilirubin

Combined elevations of aminotransferases and bilirubin, either serious or nonserious and whether or not causally related, as a potential case of Hy's Law (alanine aminotransferase [ALT] or aspartate aminotransferase [AST]  $\geq 3 \times$  upper limit of normal [ULN] and blood bilirubin  $\geq 2 \times$  ULN, with no increase in alkaline phosphatase (ALP), in the absence of other factors for the increases in both aminotransferases and total bilirubin), even when evaluated to be due to disease progression by the investigator or subinvestigator, should always be reported to the sponsor using the eCRF, with the investigator's or subinvestigator's evaluation of seriousness, causality, and a detailed narrative. This event should be reported within 24 hours of the investigator's or subinvestigator's awareness of the event.

If study drug administration is permanently discontinued due to liver enzyme abnormalities, the subject will be followed as described in Section 5.8 until the AE recovers or resolves to the condition

Confidential

before the occurrence of the AE and disappears, AE is recovering or resolving, or AE is stabilized in order to determine the nature and severity of the potential liver injury.

#### 9.4.2 Antibody Dependent Enhancement

If exacerbation of respiratory symptoms is suspected, such as pneumonia, after study drug administration, tests necessary for diagnosing SARS-CoV-2 infection (eg, RT-PCR, antigen test) will be performed wherever possible to determine whether it is caused by ADE due to SARS-CoV-2 vaccination. If the exacerbation is diagnosed as ADE due to study drug administration, it should be recorded as an AE in the eCRF. In addition, to examine the relation with ADE, blood sampling will be performed as promptly as possible, to cryopreserve serum.

#### 9.5 Investigational Device or Investigational Combination Product Defects/Regenerative Medicine Products Defects

Not applicable.

#### 9.6 Reporting of Serious Adverse Events: Procedures for the Investigator or Subinvestigator

The types of events listed below should be reported by the investigator or subinvestigator to the sponsor using the EDC, promptly after becoming aware of relevant information (within 24 hours of awareness).

The investigator should also report the detail of the event in writing promptly to the sponsor and the head of the study site. The written report to the head of the study site should be made in accordance with the procedures and format specified by the study site.

- SAEs (See Section 9.3.2 for definitions.)
- Combined elevations of aminotransferases and bilirubin, either serious or nonserious, as a potential case of Hy's Law (See Section 9.4.1 for details.)

All events (serious and nonserious) that fall under either of the above categories should be reported with the investigator's or subinvestigator's evaluation of the seriousness, severity, and causality with the study drug. A detailed narrative that summarizes the course of the event, including its evaluation, treatment, and outcome, should also be submitted. Specific or estimated dates of event onset, treatment, and resolution should be included when available. Medical history, concomitant medications, and clinical laboratory data that are relevant to the event should also be summarized in the narrative. For fatal events, the narrative should state whether an autopsy was or will be performed, and include the results if available. Source documents (including medical reports) will be retained at the study site and need not be submitted to the sponsor for the purpose of SAE reporting.

Upon receipt of urgent safety queries from the sponsor, the investigator or subinvestigator must follow and address them promptly. Follow-up information and responses to non-urgent safety queries

Confidential

should be combined for reporting to provide the most complete data possible in the eCRF.

In situations where EDC is not available, the paper serious adverse event report (SAVER) form should be completed and faxed or emailed along with the fax transmission form provided to the sponsor clinical safety and pharmacovigilance (CSPV) department. The SAVER form should be completed as soon as possible after EDC is available. For additional instructions, refer to the CRF Completion Guidelines (CCG).

See Section 15.10 for contact information for SAE reporting. If there are any questions related to SAE reporting, contact should be made to the emergency address or the monitor.

## 9.7 Notifying Regulatory Authorities, Investigators/Subinvestigators, and Institutional Review Boards/Ethics Committees

The sponsor and/or the contract research organization (CRO) will inform investigators or subinvestigators, institutional review boards/ethics committees (IRBs/ECs), and regulatory authorities of any suspected unexpected serious adverse reactions (SUSARs) occurring at a study site of this study or a study site of other studies using investigational products containing the same ingredients, as appropriate per local reporting requirements.

The sponsor and/or the CRO will comply with any additional local safety reporting requirements. To judge "Unexpected (unknown)," the section of "Reference Safety Information" in the updated IB or the document describing the latest scientific knowledge about the study drug should be referred to.

## 9.8 Exposure in Utero

The sponsor must be notified of any subject who becomes pregnant within 28 days from the study drug administration.

The sponsor must be notified of any male subject whose female partner becomes pregnant within 28 days from the study drug administration to the male subject.

Although pregnancy is not technically an AE, all pregnancies must be followed until delivery to determine their outcome. This information is important for both drug safety and public health concerns. It is the responsibility of the investigator or subinvestigator to report any pregnancy in a female subject or a male subject's female partner using the Exposure In Utero (EIU) Reporting form. Please contact your monitor to receive the EIU Reporting Form upon learning of a pregnancy. The investigator or subinvestigator should make every effort to follow the subject or the subject's partner until completion of the pregnancy and complete the EIU Reporting Form with complete pregnancy outcome information, including normal delivery and induced abortion. The outcome of the pregnancy, whether serious or nonserious, should be reported to the sponsor. If the outcome of the pregnancy meets the criteria for immediate classification as an SAE (ie, post-partum complications, spontaneous or induced abortion, stillbirth, neonatal death, or congenital anomaly, including that in miscarriage or an aborted fetus), the investigator or subinvestigator should follow the procedures for reporting SAEs

Confidential

outlined in Section 9.6.

For reports of pregnancy in the female partner of a male subject, the EIU form (or SAE form if associated with an adverse outcome) should be completed with the subject numbers, initials, and date of birth, and details regarding the female partner should be entered in the narrative section.

## 9.9 Clinical Laboratory Evaluations

The following items will be measured:

The presence or absence of measurement and the date of measurement will be recorded in the eCRF.

- Hematology test  
Red blood cell count, hemoglobin, hematocrit, white blood cell count, differential white blood cell count (neutrophils, lymphocytes, monocytes, eosinophils, and basophils), and platelet count
- Blood chemistry test  
Total protein, albumin, total bilirubin, direct bilirubin, AST, ALT, ALP, gamma-glutamyltransferase ( $\gamma$ -GT), creatine kinase (CK), blood urea nitrogen (BUN), creatinine, Na, K, Cl, total cholesterol, and triglyceride
- Urinalysis  
Sugar, protein, occult blood, and urobilinogen

## 9.10 Vital Signs

The following items will be measured:

- Axillary body temperature  
The subject or legal representative will measure the axillary body temperature of the subject every day for 7 days after study drug administration (Day 1 to Day 8) and record the results in the electronic diary. On the day of study drug administration (Day 1), axillary body temperature will be measured once on the day. On Day 2 to Day 8, axillary body temperature will be measured once a day. If it is measured at multiple times a day, the maximal body temperature will be recorded. The temperature should not be taken immediately after eating, exercising, or taking a bath.

## 9.11 Electrocardiograms

Not applicable.

## 9.12 Physical Examinations

Not applicable.

### 9.13 Other Examinations

Not applicable.

## 10. OTHER EVALUATIONS

### 10.1 Patient-Reported Outcome

Among the AEs in Section 9.3, solicited AEs will be evaluated based on the patient-reported outcome obtained from the electronic diary.

## 11. STATISTICAL METHODS

### 11.1 General Statistical Considerations

The study population consists of the following 4 sub-population:

- Sub-population A: Population with a history of SARS-CoV-2 infection\* and vaccination with SARS-CoV-2 vaccine
- Sub-population B: Population with a history of SARS-CoV-2 infection but without a history of vaccination with SARS-CoV-2 vaccine
- Sub-population C: Population without a history of SARS-CoV-2 infection but with a history of vaccination with SARS-CoV-2 vaccine
- Sub-population D: Population without a history of SARS-CoV-2 infection or vaccination with SARS-CoV-2 vaccine

\*: The history of SARS-CoV-2 infection will be based on the self-reported SARS-CoV-2 infection history at informed consent and the SARS-CoV-2 antibody test result as measured at the central laboratory at the time of eligibility evaluation.

The primary endpoint of this study will be verified in subject population with at least either a history of SARS-CoV-2 infection or vaccination with SARS-CoV-2 vaccine (ABC combined) if the following conditions are met simultaneously:

- The lower limit of 2-sided 95% confidence interval of GMT ratio (DS-5670d group vs. Comirnaty RTU IM group) for blood neutralizing activity against SARS-CoV-2 (Omicron strain XBB.1.5.6) at 4 weeks after study drug administration is greater than 0.67.
- The lower limit of 2-sided 95% confidence interval of the difference in seroresponse rate (DS-5670d group – Comirnaty RTU IM group) for blood neutralizing activity against SARS-CoV-2 (Omicron strain XBB.1.5.6) at 4 weeks after study drug administration is greater than –10%.

In addition, the key secondary endpoints of this study will be validated in subject population with or without a history of SARS-CoV-2 infection or vaccination with SARS-CoV-2 vaccine (ABCD combined) if the following conditions are met simultaneously:

- The lower limit of 2-sided 95% confidence interval of GMT ratio (DS-5670d group vs. Comirnaty RTU IM group) for blood neutralizing activity against SARS-CoV-2 (Omicron strain XBB.1.5.6) at 4 weeks after study drug administration is greater than 0.67.
- The lower limit of 2-sided 95% confidence interval of the difference in seroresponse rate (DS-5670d group – Comirnaty RTU IM group) for blood neutralizing activity against SARS-CoV-2 (Omicron strain XBB.1.5.6) at 4 weeks after study drug administration is greater than –10%.

Multiplicity of the test associated with multiple non-inferiority hypotheses in multiple populations (ABC combined and ABCD combined) will be controlled by fixed sequence testing. First, the non-

Confidential

inferiority of the DS-5670 group to the Comirnaty RTU IM group will be tested in the ABC combined population, and only if the non-inferiority is confirmed, the non-inferiority of the DS-5670d group to the Comirnaty RTU IM group will be verified in the ABCD combined population. All hypotheses will be evaluated at a one-sided 2.5% significance level.

With reference to the PMDA notification "Principles for the Evaluation of Vaccines Against the Novel Coronavirus SARS-CoV-2, (Appendix 4) Immunogenicity-based evaluation of variant vaccines modified from parent vaccines and booster vaccines with new active ingredients," the non-inferiority margins for the GMT ratio and the difference in the seroresponse rate are set at 0.67 and -10%, respectively.

In this study, analyses will be performed twice. The first analysis will be the primary analysis of immunogenicity and safety. The primary immunogenicity and safety endpoints will be evaluated to verify the non-inferiority of DS-5670d group to Comirnaty RTU IM group once when immunogenicity and safety data are collected for all subjects for 4 weeks after study drug administration or when the study is terminated. The second analyses will be performed when or the immunogenicity and safety data for 26 weeks after study drug administration have been obtained for all subjects or the study termination.

Unless otherwise specified, continuous variables will be summarized by presenting the number of subjects, arithmetic mean, standard deviation, minimum, median, and maximum, and categorical variables will be summarized by calculating the frequency and proportion. Unless otherwise specified, baseline values from each subject will be the last observed values that are available before study drug administration. Changes from baseline (eg, change, shift table) will be analyzed in subjects whose baseline values and at least one post-treatment value are available. An outline of the statistical analyses is provided below. Statistical methods will be specified in more details in separately prepared Statistical Analysis Plan (SAP).

## 11.2 Analysis Sets

Subjects with major GCP violations (violation of informed consent obtainment and significant violations of study procedures) will be excluded from all analysis sets.

- All subjects enrolled in the study must have signed the informed consent form by the subjects or legal representatives.
- All randomized subjects must have signed the informed consent form by the subjects or legal representatives.
- The safety analysis set will consist of all subjects who have signed the informed consent form by the subjects or legal representatives and received at least one dose of study drug.
- The solicited safety analysis set will consist of all subjects with at least one available data on presence or absence of occurrence of solicited AE in the safety analysis set.

Confidential

- The full analysis set (FAS) will consist of randomized subjects who meet the following criterion:
  - 1) Having received at least one dose of the study drug.
- The per-protocol set (PPS) will consist of subjects included in the FAS who meet all of the following criteria:
  - 1) Having no significant protocol violations that may affect the efficacy evaluation (eg, violation of inclusion/exclusion criteria, prohibited concomitant medications/therapies, violation of withdrawal/discontinuation criteria).
- The FAS for immunogenicity evaluation (FAS for Immunogenicity) will consist of subjects included in the FAS who meet the following criterion:
  - 1) Having immunogenicity measurements before study drug administration and at least one immunogenicity measurement after study drug administration.
- The PPS for immunogenicity evaluation (PPS for Immunogenicity) will consist of subjects included in the FAS for Immunogenicity who meet the following criterion:
  - 1) Having no significant protocol violations that may affect the immunogenicity evaluation (eg, violation of inclusion/exclusion criteria, prohibited concomitant medications/therapies, violation of withdrawal/discontinuation criteria).
- The FAS with basic immunity (Immunized FAS) will consist of subjects included in the FAS who meet the following criterion:
  - 1) Having at least either a history of SARS-CoV-2 infection\* or vaccination with SARS-CoV-2 vaccine and completed the study drug administration as specified in the protocol.

\*: The history of SARS-CoV-2 infection will be based on the self-reported SARS-CoV-2 infection history at informed consent and the SARS-CoV-2 antibody test result as measured at the central laboratory at the time of eligibility evaluation. The subject will be defined as having a history of SARS-CoV-2 infection based on self-reported SARS-CoV-2 infection history at informed consent or as having had a positive SARS-CoV-2 antibody test as measured at the central laboratory at the time of eligibility evaluation. Otherwise, the subject will be defined as having no history of SARS-CoV-2 infection.
- The per-protocol set with basic immunity (Immunized PPS) will consist of subjects included in the Immunized FAS who meet the following criterion:
  - 1) Having no significant protocol violations that may affect the efficacy evaluation (eg, violation of inclusion/exclusion criteria, prohibited concomitant medications/therapies, violation of withdrawal/discontinuation criteria).
- The FAS with basic immunity for immunogenicity evaluation (Immunized FAS for Immunogenicity) will consist of subjects included in the Immunized FAS who meet the following criterion:
  - 1) Having immunogenicity measurements before study drug administration and at least one

Confidential

immunogenicity measurement after study drug administration.

- The PPS with basic immunity for immunogenicity evaluation (Immunized PPS for Immunogenicity) will consist of subjects included in the Immunized FAS for Immunogenicity who meet the following criterion:
  - 1) Having no significant protocol violations that may affect the immunogenicity evaluation (eg, violation of inclusion/exclusion criteria, prohibited concomitant medications/therapies, violation of withdrawal/discontinuation criteria).

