#### 11.4.1 Primary Efficacy Analysis

The following analyses will be performed for the Immunized PPS for Immunogenicity.

The GMT ratio (DS-5670d group vs. Comirnaty RTU IM group) for blood neutralizing activity against SARS-CoV-2 (Omicron strain XBB.1.5.6) at 4 weeks after study drug administration and its 2-sided 95% confidence interval will be calculated by administration arm. The difference in seroresponse rate (DS-5670d group – Comirnaty RTU IM group) for blood neutralizing activity against SARS-CoV-2 (Omicron strain XBB.1.5.6) at 4 weeks after study drug administration and its 2-sided 95% confidence interval will be calculated.

A linear model will be applied with blood neutralizing activity against SARS-CoV-2 (Omicron strain XBB.1.5.6) at 4 weeks after study drug administration as an explained variable, administration

Confidential

arm as an explanatory variable, and baseline value (common logarithmic value), a history of SARS-CoV-2 infection and vaccination with SARS-CoV-2 vaccine as covariates, based on which the GMT ratio (DS-5670d group vs. Comirnaty RTU IM group) and its 2-sided 95% confidence interval will be calculated. The covariates may be changed depending on subject enrollment.

In addition, the difference in seroresponse rate (DS-5670d group – Comirnaty RTU IM group) for blood neutralizing activity against SARS-CoV-2 (Omicron strain XBB.1.5.6) at 4 weeks after study drug administration and its 2-sided 95% confidence interval will be calculated. This analysis may be changed to stratified analysis depending on subject enrollment.

DS-5670d will be judged to be non-inferior to Comirnaty RTU IM if the lower limit of 2-sided 95% confidence interval in adjusted GMT ratio (DS-5670d group vs. Comirnaty RTU IM group) is greater than 0.67 and simultaneously the lower limit of 2-sided 95% confidence interval of the difference in seroresponse rate (DS-5670d group – Comirnaty RTU IM group) is greater than –10%.

The same supplementary analyses will also be performed for the Immunized FAS for Immunogenicity.

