#### 11.4.5 Safety Analysis

Solicited AEs will be analyzed in the solicited safety analysis set, and other safety analyses will be performed in the safety analysis set. The analyses will be performed based on the study drug that was actually administered to each subject.

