## 15.5 Protocol Deviations

The investigator or subinvestigator should conduct the study in compliance with the protocol agreed to by the sponsor and, if required, by regulatory authorities, and approved by the IRB/EC.

A deviation from any protocol procedures or waiver to any stated criteria will not be allowed in this study except where necessary to eliminate immediate risks to the subject. The sponsor must be promptly notified of all intended or unintended deviations from the protocol (eg, inclusion/exclusion criteria, study drug administration, missed study visits).

The investigator or subinvestigator should document and explain any deviation from the approved protocol.

If a subject was ineligible for the study or received an incorrect dose or treatment, but had at least one dose of the study drug, data of the subject must be collected for safety purposes.

If applicable, the investigator should notify the IRB or EC of deviations from the protocol in accordance with local procedures.

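### Section 11.2 removes subjects with major GCP violations, including procedural ones, from every analysis set, so a consented, vaccinated subject can drop out of the safety tables and of the FAS check

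*Protocol*

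**What the plan says.** The opening sentence of Protocol section 11.2 governs every set that follows: "Subjects with major GCP violations (violation of informed consent obtainment and significant violations of study procedures) will be excluded from all analysis sets". The definitions beneath it include:

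- Safety analysis set: "The safety analysis set will consist of all subjects who have signed the informed consent form" (or whose representatives signed) and who received at least one dose. The solicited safety analysis set is the part of it with some diary data on solicited events.
- FAS: randomized subjects with one criterion, "Having received at least one dose of the study drug".
- PPS for Immunogenicity and its immunized counterpart: the corresponding FAS for Immunogenicity, subject to "Having no significant protocol violations that may affect the immunogenicity evaluation". The examples given are breaches of eligibility, of prohibited medication or therapy, and of withdrawal criteria.
- Immunized FAS: FAS members with prior infection or vaccination who also completed administration in the way the protocol prescribes.

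Section 11.4.5 assigns the safety work: "Solicited AEs will be analyzed in the solicited safety analysis set, and other safety analyses will be performed in the safety analysis set". It adds: "The analyses will be performed based on the study drug that was actually administered to each subject". For the primary comparison, section 11.4.1 says "The following analyses will be performed for the Immunized PPS for Immunogenicity" and repeats the analysis in the Immunized FAS for Immunogenicity as supplementary.

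**The concern.** The opening sentence applies one consequence to two different situations. A subject without valid consent has no place in any set. A subject who consented and was vaccinated, but whose conduct or handling involved a serious procedural breach, was still exposed to the vaccine. What happened to that subject is safety information. Procedural breaches belong to the per-protocol definition, which already has a criterion for them.

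Two things are at stake. First, such a subject's events are absent from the solicited, unsolicited, serious event and laboratory summaries because of a judgement about conduct rather than exposure. Second, the full analysis set is the only set offered beside the per-protocol one for the non-inferiority analysis. A subject removed from both cannot contribute to showing whether the exclusion mattered.

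**Working it through.** **Planned figures.** No stated figure depends on this rule. The power in section 11.6 reproduces: n = 690 × 0.9 / 2 = 310.5, taken as 310 per arm, with one-sided 0.025.
- GMT: −log10(0.67) = 0.1739; standard error 0.533 × √(2/310) = 0.0428; 0.1739/0.0428 − 1.96 ≈ 2.10, giving 98.2% (98.2% with the noncentral t as well).
- Seroresponse at 80% in both arms with a 10-point margin: 87.2% by Farrington–Manning.
- Product: 85.6%.

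All three match the Protocol.

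**Safety sets.**
1. The opening rule of 11.2 covers all sets, and two of those it precedes are the safety and solicited safety sets.
2. Section 11.4.5 runs all safety analyses in those two sets and no other.
3. So a consented, dosed subject classed as a major GCP violator on procedural grounds is in no safety table.
4. The safety set definition in the same section asks only for signed consent and one dose. The consent half of the opening rule agrees with it; the procedural half does not.

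**Efficacy sets.**
1. The per-protocol sets are subsets of the full analysis sets, and the opening rule cuts both.
2. A subject cut by that rule is therefore missing from the primary and the supplementary analysis alike.
3. A second route has the same effect. The Immunized FAS requires administration as the protocol prescribes, so a subject dosed otherwise leaves the supplementary set even if the opening rule is rewritten. The unrestricted FAS has no such clause.

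**Size (illustration only).** The Protocol gives no rate of major GCP violations. Assume that a share of the 345 subjects per arm (section 11.6) is so classified, that the event has 1% incidence, and that exclusion is unrelated to events. The chance that at least one affected subject is lost from an arm is 1 − 0.99^k, where k is the number excluded:

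- 1% excluded: k = 3, chance 3.0%
- 2% excluded: k = 7, chance 6.8%
- 5% excluded: k = 17, chance 15.7%

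For one lost case, take 395 per arm (790/2, using the 100 subjects assumed for Sub-population D in section 11.6). A single event is 1/395 = 0.25%, with exact upper 97.5% limit 1.40%. Without that subject it is 0/394, with upper limit 1 − 0.025^(1/394) = 0.93%. This shows what losing one case does; it does not show that a case would be lost.

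**The case against.** The strongest reply is that the trigger is narrow. It is a major GCP violation, not any significant protocol violation, and section 15.8 lists major GCP violations and major protocol deviations as separate things. The per-protocol criterion uses a different term, a different threshold and its own examples. A general exclusion followed by definitions is also a normal layout, and an SAP may define the class. The point about narrowness stands and limits the number affected. It does not remove the conflict: the parenthesis expressly brings procedural violations into the class, and a definition of the class would not make the consequence fit the safety set definition.

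A reader might infer more, and the text does not support it:

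- *That ineligible or wrongly dosed subjects are dropped from safety.* Section 15.5 says of them that "data of the subject must be collected for safety purposes", and section 6.2 has dosing errors recorded. Both concern collection and recording, not analysis sets. Nothing classes these cases as major GCP violations, and 11.2 names eligibility breaches as a per-protocol matter.
- *That analysis by drug received contradicts the rule.* It does so only if a dosing error is itself classed as a major GCP violation, which no section says.
- *That the events vanish altogether.* SAE recording and 24-hour reporting (9.2, 9.6) do not depend on analysis sets, and 11.3 tabulates exclusions with reasons. What 11.3 does not show is the excluded subjects' events.
- *That exclusions would favour one arm.* Storage and preparation differ between the vaccines, so imbalance is conceivable, but the Protocol gives no rates to support it.

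**Conclusion.** The point holds in limited form and should be fixed. As written, section 11.2 lets a procedural finding remove a consented, vaccinated subject from the safety analyses, against its own safety set definition, and from both efficacy families, so that the supplementary analysis cannot show the effect of that removal. This follows from 11.2 read with 11.4.1 and 11.4.5 and needs no assumption about rates.

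Its size does need assumptions. The count is unknown and probably small, and the figures of 3.0% to 15.7% rest on assumed exclusion shares, an assumed 1% incidence and exclusion unrelated to events. The primary analysis set, the margins and the planned power are not in question, and safety is summarised descriptively. It would go too far to say that the full analysis set and the per-protocol set lose the same subjects in general: they do so only for the class caught by the opening rule and, in the immunized population, for subjects not dosed as prescribed.

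**What to change.** In section 11.2, and in the SAP to match:

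1. Limit exclusion from all analysis sets to subjects without valid informed consent.
2. State that every consented subject who received study drug stays in the safety analysis set, analysed by drug received, and that every randomized, dosed subject with valid consent stays in the FAS, analysed as assigned.
3. State that significant violations of study procedures lead to exclusion from the per-protocol sets only, under criteria fixed before unblinding. Section 11.7 already requires the SAP to be final by then.
4. Move the requirement for protocol-conforming administration from the Immunized FAS to the immunized per-protocol sets. Attach it to both the Immunized PPS and the Immunized PPS for Immunogenicity. The latter is built from the Immunized FAS for Immunogenicity and would otherwise lose the condition. Without this step, rewriting the opening sentence would not bring wrongly dosed subjects back into the set that checks the primary analysis.

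The cost is a few sentences of text. No new data, visits or subjects are needed, and the power calculation does not change.
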